#### Exploratory objectives

2.2.4

Exploratory objectives include the acceptance and practicability of smartwatches for AFib detection (assessment of patient responses via self-designed questionnaire with ordinal items), AFib burden/ patient, AFib risk factors, AFib detection rates after 1, 3, and 6 months, time to confirmed AFib diagnosis, and count of AFib diagnoses.

### Data monitoring body

2.3

The Muenchner Studienzentrum (MSZ), an independent clinical research institution at the School of Medicine and Health, Technical University Munich, is responsive for quality assurance. Monitoring activities are performed to ensure that the study is conducted in accordance with the protocol.

### Sample size estimation

2.4

According to a previous study a sensitivity and specificity for AFib detection per patient of >99 and 90%, can be assumed, respectively (18). Thus, 40 cases of AFib are required to estimate the sensitivity with a precision of about 10%, i.e., the difference of the lower bound of a two-sided exact 95% confidence interval and the point estimate of the sensitivity is 10%. As other studies observe paroxysmal AFib in 9%−16% of patients with cryptogenic stroke (4, 5), we intend to enroll 400 patients to obtain the required 40 cases. The specificity can consequently be measured with a precision of 4%. Our inclusion criteria should lead to a preselection of candidates with increased AFib risk factors. Therefore, AFib detection rate might increase up to 28% (max = 112) in our cohort within 6 months (8). The event of a 10% drop-out rate (e.g., due to withdrawal of consent, eligibility violations, no intervention, or non-existent data after inclusion into the study) would result in a minimum of 36 AFib cases and a similar precision of estimation i.e., 12% for the sensitivity and 4% for the specificity.

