As stroke patients often suffer from relevant disabilities, a transfer from the hitherto existing data about AFib and smartwatches from otherwise healthy individuals cannot be assumed. To our knowledge, there is only one other ongoing study assessing the accuracy of smartwatch-derived PPG signal for AFib detection in a stroke population under real-life circumstances (NCT05006105). So far, the protocol or final results have not been published.

We hypothesize that AFib detection via smartwatch in patients suffering from cryptogenic transient ischemic attack (TIA) or ischemic stroke is accurate for AFib detection compared to an implantable Event Recorder and hence introduce the following prospective multi-center clinical trial (WATCH AFib). If our hypothesis proves right, smartwatches might be a non-invasive, cost-effective, widely available alternative for rhythm monitoring, which could potentially change the current standard of post-stroke care.

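### The stated minimum of 36 AFib cases after drop-out is an expected count at an unstated 10% rate; the protocol's own lower rate of 9% gives about 32

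*Protocol article*

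**What the plan says.** All the planning figures are in the protocol article, section 2.4 (Sample size estimation).

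- **Accuracy assumed:** "a sensitivity and specificity for AFib detection per patient of >99 and 90%, can be assumed, respectively", taken from one previous study.
- **Target:** "40 cases of AFib are required to estimate the sensitivity with a precision of about 10" percent. Precision is the distance from the point estimate down to the lower limit of a two-sided exact 95% confidence interval.
- **Enrolment:** after citing AFib in 9% to 16% of cryptogenic strokes, the article says "we intend to enroll 400 patients to obtain the required 40 cases". It adds that the risk-factor criteria might raise detection to as much as 28% (112 cases).
- **Drop-out:** a 10% loss "would result in a minimum of 36 AFib cases and a similar precision of estimation", namely 12% for sensitivity and 4% for specificity.

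Section 2.5 (Statistical methods and analysis populations) treats the number of AFib cases as the effective sample size. It starts the analysis either at 40 cases with completed follow-up or when all 400 patients have finished, whichever comes first. In the full analysis set, missing smartwatch values count as no AFib signal. Patients with no intervention or no data are excluded, and a per-protocol analysis is also planned.

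**The concern.** A minimum should be either the count at the bottom of the planning range or a floor that the trial is very unlikely to fall below. The figure of 36 is neither. The article moves from a range of 9% to 16% to a count of 40 without saying which rate it used. Only 10% links 400 to 40 and 360 to 36, and that rate lies above the lower end of the cited range.

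This matters because the number of AFib cases drives the precision of sensitivity, which is half of the primary objective. A reader would take 36 cases and 12% as the worst that the design can produce. The second analysis trigger in section 2.5 allows the trial to finish with fewer than 40 cases, so a low count could occur in practice.

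**Working it through.** **Inputs (section 2.4):** 400 enrolled; 10% drop-out, leaving 400 × 0.90 = 360; AFib rate 9% to 16%, possibly up to 28%; sensitivity >99%; specificity 90%; two-sided exact (Clopper-Pearson) 95% interval.

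**Step 1: reproduce the printed figures.**

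Cases = patients × rate. At 10%, 400 × 0.10 = 40 and 360 × 0.10 = 36. Both printed counts follow from this unstated rate.

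For x detected among n cases, the lower limit L is the 2.5% quantile of a Beta(x, n − x + 1) distribution, and precision = x/n − L.

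- 40 cases: 39/40 gives 0.975 − 0.868 = 10.7 points; 40/40 gives 8.8; a sensitivity of 99% on a continuous scale gives 9.7. All fit a target of about 10%.
- 36 cases: 35/36 gives 0.972 − 0.855 = 11.8 points, which rounds to the printed 12%; 36/36 gives 9.7; 99% on a continuous scale gives 10.6. Only the one-miss case reproduces 12%.
- Specificity at 90%: 324/360 gives 3.6 points, and 292/324 (after drop-out) gives 3.8. Both round to the printed 4%.

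The printed 10%, 12% and 4% therefore follow from the plan's own inputs.

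**Step 2: case counts over the cited rates, with the chance of reaching the stated counts (binomial).**

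| AFib rate | Cases in 400 | Cases in 360 | P(≥40 of 400) | P(≥36 of 360) |
|---|---|---|---|---|
| 9% | 36 | 32.4 | 27% | 28% |
| 10% | 40 | 36 | 52% | 53% |
| 16% | 64 | 57.6 | >99.9% | >99.9% |
| 28% | 112 | 100.8 | >99.9% | >99.9% |

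At 9% the required 40 is missed in expectation before any patient drops out. At 10% the supposed minimum is missed nearly half the time (100% − 53% = 47%); at 9% it is missed about 72% of the time.

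**Step 3: precision for sensitivity with 32 cases.**

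- No miss, 32/32: 1 − 0.891 = 10.9 points.
- 99% on a continuous scale: 11.7 points.
- One miss, 31/32: 0.969 − 0.838 = 13.1 points.

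On the one-miss convention that gives the printed 12%, the low end is 13.1 against 11.8, a loss of about 1.3 points. Specificity is unaffected: 360 − 32 = 328 patients without AFib, and 295/328 gives 3.8 points.

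**Step 4: sensitivity below 99%.** The article gives no sensitivity adjusted for missing smartwatch data, so the 95% used here is an assumption. At 95%, precision is 11.9, 12.9 and 14.0 points for 40, 36 and 32 cases.

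**The case against.** The strongest reply is that 9% is the bottom of a literature range for cryptogenic stroke in general, not the rate expected here. Every participant needs at least one AFib risk factor, and the article expects this to raise detection. The chance of at least 36 cases in 360 is 75% at a rate of 11%, 90% at 12% and 94% at 12.5%, the midpoint of the range. This stands: the shortfall arises only near the bottom of the range. It does not rescue the word minimum, because a hoped-for higher rate cannot set a floor.

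Three stronger readings are tempting, and the document supports none of them.

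- **That the 10% to 12% precision is not delivered.** The printed figures reproduce, and at 99% sensitivity even 32 cases give 11.7 points. The wider 13.1 needs one miss in 32, an observed sensitivity of 96.9%. The lower case count alone costs about one point.
- **That the full-analysis-set rule contradicts the sensitivity above 99%.** Detection is judged per patient, so one detected episode in six months is enough, and unworn time makes a miss only if all of that patient's AFib escapes the recorded time. Patients without data are excluded, not scored as misses, and a per-protocol analysis is planned. The rule can lower sensitivity, which makes >99% optimistic, but that is not a contradiction.
- **That the Introduction disowns the sensitivity input.** It says that "a transfer from the hitherto existing data about AFib and smartwatches from otherwise healthy individuals cannot be assumed". The article does not describe the population of the study behind the >99%, so the text does not show that this caution applies to it.

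It is also fair that the primary analysis is estimation with no accuracy threshold, so one point of precision changes no decision rule.

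**Conclusion.** The point holds as a minor correction of a stated figure. The 36 cases are the expected count at an unstated 10% rate. The document's own lower rate gives 36 cases before drop-out, short of the required 40, and about 32 after it. The chance of at least 36 cases after drop-out is about 28% at 9% and 53% at 10%. The low-end precision for sensitivity is about 13% on the convention that yields the printed 12%, or 10.9% with no miss. The printed specificity precision of 4% stands.

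The counts and chances assume that AFib cases follow a binomial distribution and that exactly 10% of patients drop out regardless of AFib status. Precision at sensitivities below 99% is illustrative only, because the article gives no basis for a particular value.

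**What to change.** In section 2.4:

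1. State that 10% is the planning rate that links 400 patients to 40 cases.
2. Replace the minimum of 36 with expected counts after 10% drop-out: about 32 at 9%, 36 at 10%, 58 at 16% and 101 at 28%.
3. Give the low-end precision for sensitivity as about 13% (31 of 32 detected), with 10.9% if no case is missed. Keep 4% for specificity.
4. Optionally, note that >99% is optimistic for the full analysis set, where missing smartwatch values count as no AFib signal, and that precision widens if sensitivity is lower. The 95% row (11.9, 12.9 and 14.0% for 40, 36 and 32 cases) would serve, labelled as an assumption.

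The cost is a few words and a slightly less favourable low-end precision. Enrolment, analysis triggers and methods stay as they are.

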### Statistical methods and analysis populations

2.5

Point estimates and two-sided exact 95% confidence intervals will be computed for the sensitivity and specificity referring to the primary objectives, related secondary objectives and subgroup analyses. Cardiologist-supervised event recorder-based continuous ECG rhythm analysis serves as the gold standard. Thus, in the case of discordant results, we consider the analysis of the signal from the event recorder by the cardiologist as the true status. As power calculation is based on participants with detected AFib as effective sample size (n_AFib_), we intend on analyzing our data as soon as one of the following situations occurs: (1) AFib is detected in 40 participants, who have completed follow-up or (2) enrolment and follow up is complete for all 400 participants (n_Enrolment_). In the first situation, the study leadership, the statistician, and the steering committee will decide on continuation of enrolment. Exploratory hypothesis testing of comparisons will be performed by McNemar's Chi-squared Test at two-sided 5% levels of significance. Due to the exploratory character of the analysis, and in accordance with the calculation of 95% confidence intervals, there will be no correction for multiple testing. With reference to the ICH E9 Guideline, the analyses will be performed using a full analysis set (FAS), according to the intention-to-treat principle (ITT), and a per protocol set (PP). The former will include all times with event recorder measurements (until possible but unexpected losses to follow-up) and the latter will include only times with additional smartwatch recordings. Therefore, missing values, possibly due to non-compliance, will be rated as no signal of an AFib by the smartwatch in the FAS. The FAS and PP analysis populations coincide when smartwatch records are available in all patients. Patients with eligibility violations (concerning inclusion or exclusion criteria), no intervention or non-existent data after inclusion into the study will be excluded from analysis. Time to confirmed AFib diagnosis, count of AFib diagnoses, AFib burden, safety endpoints and usability of smartwatches will be reported by descriptive statistics (mean, standard deviation, median, interquartile range, absolute and relative frequency). AFib risk factors will be compared between patient groups with and without AFib using descriptive statistics, hypothesis testing and multiple logistic regression models. Pre-defined subgroup analyses will be performed as described above.

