#### Primary objectives

2.2.1

The primary objective is to assess whether AFib detection via smartwatch in patients suffering from cryptogenic TIA/ischemic stroke is accurate in comparison to implantable event recorders. This will be assessed by sensitivity and specificity of AFib detection per patient after 6 months. We aim on a comparison of smartwatch based, continuous, automated, cardiologist supervised rhythm analysis of photoplethysmography (PPG)- signal and patient activated one-lead ECG with event recorder based, continuous, automated ECG rhythm analysis.

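### Exact binomial intervals are assigned to episode- and time-level accuracy measures, where units from one patient are not independent; these secondary intervals would be too narrow by an amount that depends on the unit

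*Protocol article*

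**What the plan says.** Section 2.5 (Statistical methods and analysis populations) gives a single rule: "Point estimates and two-sided exact 95% confidence intervals will be computed for the sensitivity and specificity referring to the primary objectives, related secondary objectives". The sentence goes on to include the subgroup analyses. No other interval method appears in the article, and clustering by patient is not mentioned.

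The primary endpoint is one result per patient: "This will be assessed by sensitivity and specificity of AFib detection per patient after 6 months". The sample size in section 2.4 is also per patient. It defines precision through the exact interval: "the difference of the lower bound of a two-sided exact 95% confidence interval and the point estimate of the sensitivity is 10" percent.

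Section 2.2.3 (Secondary objectives) contains per-patient measures (predictive values, automated PPG analysis) and four sensitivity or specificity measures on other units:

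- any AFib episode
- AFib episodes longer than 1 h
- sinus-rhythm episodes longer than 1 h
- recorded or analyzable time

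Two further statements in section 2.5 bear on the point. It treats the number of participants with AFib as the effective sample size. In the full analysis set (FAS) it scores missing smartwatch data as no AFib signal.

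**The concern.** An exact binomial interval is valid when each unit is an independent success or failure. One classification per patient meets that condition. Episodes and time intervals do not, because wear habits, signal quality and neurological deficit are shared by all units from the same patient. The article expects such patient-level influences, since section 2.2.2 predefines subgroups on the ground that deficits may impair use of the watch.

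The FAS rule adds to this. If a patient stops wearing the watch while the event recorder keeps running, every later AFib episode in that patient counts as missed. Failures then arrive in blocks by patient.

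At stake is the stated precision of four secondary accuracy measures. A naive interval treats hundreds of episodes, or very many hours, as that many independent observations, although they come from about 40 AFib patients (or about 360 without AFib).

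**Working it through.** **1. Which exact interval is meant.** Section 2.4 assumes "sensitivity and specificity for AFib detection per patient of >99 and 90%, can be assumed, respectively" and plans as follows: "we intend to enroll 400 patients to obtain the required 40 cases". That leaves 400 − 40 = 360 patients without AFib, or 36 and 324 after 10% drop-out. Precision is the point estimate minus the lower Clopper-Pearson limit.

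| Count | Estimate | Lower limit | Difference | Article |
|---|---|---|---|---|
| 40/40 | 100% | 91.2% | 8.8 points | about 10% |
| 39/40 | 97.5% | 86.8% | 10.7 points | about 10% |
| 35/36 | 97.2% | 85.5% | 11.8 points | 12% |
| 324/360 | 90.0% | 86.4% | 3.6 points | 4% |
| 292/324 | 90.1% | 86.3% | 3.8 points | 4% |

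The article's figures, including "a minimum of 36 AFib cases and a similar precision of estimation i.e., 12% for the sensitivity and 4% for the specificity", are reproduced. Its exact interval is the ordinary binomial one for independent units, and it is correctly used per patient.

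**2. Effect of clustering, in formula.** With m units per patient and within-patient correlation ρ, the variance is inflated by DE = 1 + (m − 1)ρ. The correct width is about √DE times the naive width, and naive coverage is about 2Φ(1.96/√DE) − 1. For geometric counts with mean m, E[m²]/E[m] = 2m − 1, so DE = 1 + (2m − 2)ρ. The article gives neither m nor ρ, so both are assumptions here.

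**3. AFib episodes.** The simulation used 40 AFib patients, patient sensitivities from a beta distribution with mean 0.90, geometric counts and 2,000 replicates per setting.

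| Mean m, ρ | DE | Coverage by formula | Simulated coverage of exact interval | Naive width | Cluster-robust width |
|---|---|---|---|---|---|
| 5, 0.05 | 1 + 8 × 0.05 = 1.4 | 90% | 92–93% | 8.8 points | 9.8 points |
| 10, 0.1 | 1 + 18 × 0.1 = 2.8 | 76% | 77–80% | 6.1 points | 9.5 points |
| 20, 0.3 | 1 + 38 × 0.3 = 12.4 | 42% | 42–45% | 4.2 points | 13.4 points |

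Ranges reflect repeat runs. At a mean of 3 episodes and ρ = 0.05, coverage was 94%. Equal counts soften the effect: 95.5% at 5 and 0.05, 84.5% at 10 and 0.1, 57% at 20 and 0.3. At true sensitivity 97.5% with geometric counts, coverage was 94.5%, 81% and 46% in the table's three settings.

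**4. Sinus-rhythm and time units.** Suppose time is cut into hours.

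- 1,000 hours per patient (assumed): DE = 1 + 999 × 0.001 = 2.0 at ρ = 0.001, and 1 + 999 × 0.01 = 11.0 at ρ = 0.01. Simulated coverage was 82% and 43%.
- Full wear for 183 days (assumed): m = 183 × 24 = 4,392, so √DE = √(1 + 4,391ρ), which is 2.3 at ρ = 0.001, 6.7 at 0.01 and 14.8 at 0.05.

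Cutting hours into minutes multiplies n by 60 and shrinks the naive interval by about √60 = 7.7 without new information.

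**5. FAS rule, illustration.** Assume 5% of AFib patients start but then do not wear the watch during their episodes, and the others detect 97%. Mean sensitivity is 0.95 × 0.97 = 0.9215. Between-patient variance is 0.05 × 0.95 × 0.97² = 0.0447, and 0.9215 × 0.0785 = 0.0723, so ρ ≈ 0.0447/0.0723 ≈ 0.6. Simulated coverage was 62% at mean 5 episodes and 45% at mean 10.

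**The case against.** **The word *related*.** The rule covers related secondary objectives, not all of them. One could read this as the per-patient ones only, which would leave the episode and time measures to a fuller document. That reading is possible. Section 2.2.3 draws no such line, however, and the four measures are themselves sensitivities and specificities. Even on the narrow reading the wording needs clarifying. On the broader one the article has fixed a method rather than left it open.

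**Size.** Someone might infer that every one of these intervals will be far too narrow. The documents do not support that for AFib episodes. The article gives no episode counts or correlation, and with few episodes and low correlation coverage stays close to nominal. At true sensitivity 97.5%, the only episode-level figure in the article (Introduction, episodes over 1 h), it was 97% at mean 3 and about 94% at mean 5 with ρ = 0.05. This part of the objection stands. It does not carry over to finely cut time.

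**Importance.** No success criterion, stopping condition or sample-size figure depends on these intervals. This stands and limits the severity.

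**Endpoint definitions.** It is tempting to add that episode-level specificity has no countable set of negatives and should be replaced. How episodes and negatives are counted is commonly settled in a fuller document. The choice of measure is separate from the interval error and is not part of this point.

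**Conclusion.** The point holds as a moderate issue for secondary objectives. Followed as written, section 2.5 attaches an independence-based interval to four measures whose units are clustered within patients, and those intervals would be too narrow.

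- **Sinus-rhythm and time units:** markedly too narrow even at correlations of 0.001 to 0.01, provided recording is cut into many units per patient, such as hours. The article does not say how it is cut. If uninterrupted sinus rhythm counted as one long episode, units per patient would be fewer and the effect smaller.
- **AFib episodes:** anything from near nominal (about 91–95% coverage at mean 3–5 episodes and correlation 0.05) to about 78% (mean 10, 0.1) and about 44% (mean 20, 0.3). These rest on 40 AFib patients, true sensitivity 90% and unequal counts.
- **FAS versions:** the missing-data rule raises within-patient correlation. The size depends on how many patients stop wearing the watch, and the 5% used above is an assumption.

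A reader might infer that the primary result or the planned 400 patients are also in doubt. They are not. Those analyses use one unit per patient and the stated precisions reproduce. The per-patient secondary measures are likewise unaffected.

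**What to change.** Reword section 2.5 so that exact binomial intervals apply only to per-patient measures, and state which secondary objectives *related* covers.

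For episode- and time-level measures, name an interval that accounts for clustering by patient and behaves well near 100% with about 40 clusters. Suitable choices are a patient-level cluster bootstrap, or a logit-scale GEE with robust variance and a small-sample correction. A plain robust Wald interval is not enough: at true sensitivity 97.5% with 10 to 50 episodes per patient it covered only about 74–92% in the simulation. Check the chosen method by simulation at high sensitivity.

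Fix the time unit, and how sinus-rhythm periods are divided, before analysis. Under section 2.5, analysis may begin once 40 participants with AFib have completed follow-up.

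The cost is a change of wording and a little programming, with no additional data or patients. The downside is wider intervals for these secondary measures.

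### The 40-case analysis trigger sets no follow-up condition for AFib-free patients, so an early analysis either mixes full and partial observation in specificity or loses the stated 4% precision

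*Protocol article*

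**What the plan says.** The primary objective (section 2.2.1) is "sensitivity and specificity of AFib detection per patient after 6 months".

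Section 2.5 gives two situations that start the analysis. The first is "analyzing our data as soon as one of the following situations occurs: (1) AFib is detected in 40 participants, who have completed follow-up". The second is "enrolment and follow up is complete for all 400 participants". For the first it adds: "In the first situation, the study leadership, the statistician, and the steering committee will decide on continuation of enrolment". It does not say what happens to enrolled patients who are still being followed.

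On the full analysis set (FAS), the same section says: "The former will include all times with event recorder measurements (until possible but unexpected losses to follow-up". The listed exclusions are eligibility violations, no intervention and no data after inclusion. Unfinished follow-up is not among them.

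Section 2.4 assumes a sensitivity above 99% and a specificity of 90%, and derives a precision of about 10% for sensitivity from 40 AFib cases and 4% for specificity from 400 patients. It cites an AFib rate of 9–16% and says that the inclusion criteria may raise it to 28%.

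**The concern.** The two situations carry different follow-up rules. The second waits for everybody. The first waits only for the AFib cases, and enrolment may still be open when it is met. Patients recruited in the preceding 6 months would then be unfinished, and most of them would be AFib-free so far.

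The endpoint is per patient, and its two components depend on observation time. The Discussion itself says that AFib detection depends on how long the rhythm is monitored. A patient with one quiet month has had less chance of a false watch alarm than one with six, and may still show AFib on the recorder later. Counting that patient as a recorder-negative for a 6-month endpoint would tend to raise specificity.

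Leaving such patients out avoids this, but shrinks the AFib-free group on which the stated specificity precision depends. The choice between the two should not be left until data may already be known.

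**Working it through.** **1. The plan's own figures.** Precision is the point estimate minus the lower limit of the two-sided exact (Clopper–Pearson) 95% interval, as section 2.4 defines it.

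- Sensitivity, 40 cases: 39/40 gives 0.975 − 0.868 = 10.7%; 40/40 gives 1 − 0.912 = 8.8%. The stated value of about 10% is reproduced.
- Sensitivity, 36 cases: 35/36 gives 0.972 − 0.855 = 11.8%, stated as 12%.
- Specificity, 360 AFib-free at 90%: 0.900 − 0.864 = 3.6%. With 324 after dropout: 3.8%. Both are stated as 4%.

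**2. When the first situation arises.** Expected completers at the trigger = 40 / AFib rate.

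- 9%: 444, more than the 400 planned. 10%: 400. On expected numbers there is no early analysis, although by chance the 40th case can come somewhat sooner.
- 16%: 40/0.16 = 250 completers, 210 of them AFib-free.
- 28%: 40/0.28 = 143 completers, 103 of them AFib-free.

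**3. If only completers are analysed.** Specificity precision at 90%:

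- 16%, n = 210: 0.900 − 0.851 = 4.9%.
- 28%, n = 103: 0.900 − 0.825 = 7.5%.

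**4. If patients in mid-follow-up are included.** This needs assumptions that are not in the article: uniform accrual of 400 patients over 12 to 48 months, a constant AFib hazard, and a false-positive risk that builds up steadily to 10% at 6 months. Write f for the fraction of the 6 months observed and r for the AFib rate. The chance of being AFib-free so far is (1 − r)^f, and the chance of no false positive is 0.9^f.

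Worked case, r = 16%, accrual over 24 months (16.7 per month, so 6 × 16.7 = 100 unfinished, f uniform on 0 to 1):

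- AFib-free so far: 100 × (1 − 0.84)/(−ln 0.84) = 91.8.
- Specificity among them: mean of 0.756^f divided by mean of 0.84^f = 0.8723/0.9177 = 0.951, where 0.756 = 0.84 × 0.9.
- Pooled: (210 × 0.90 + 91.8 × 0.951)/301.8 = 91.5%.
- Counted as AFib-free but recorder-positive by month 6: 100 × (0.9177 − 0.84) = 7.8.

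The same steps for the other cases:

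| AFib rate | Accrual (months) | Unfinished | Share of AFib-free group | Pooled specificity | Later recorder-positive |
|---|---|---|---|---|---|
| 16% | 12 | 150 | 39% | 91.5% | 8.6 |
| 16% | 24 | 100 | 30% | 91.5% | 7.8 |
| 16% | 36 | 67 | 23% | 91.1% | 5.2 |
| 16% | 48 | 50 | 18% | 90.9% | 3.9 |
| 28% | 12 | 200 | 62% | 93.2% | 26.5 |
| 28% | 24 | 100 | 45% | 92.3% | 13.2 |
| 28% | 36 | 67 | 36% | 91.9% | 8.8 |
| 28% | 48 | 50 | 29% | 91.5% | 6.6 |

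In the 16%, 12-month row, enrolment has already ended at 400 when the trigger comes. Of the 150 unfinished patients, none has less than 1.5 months of observation, so the shift is no larger than in the 24-month row.

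**5. If the analysis waits for everyone enrolled by the trigger.** AFib-free patients = enrolled × (1 − r). At 16%, 300 to 400 enrolled give 252 to 336 AFib-free and a precision of 4.4% to 3.7%. At 28%, 193 to 343 enrolled give 139 to 247 AFib-free and 6.2% to 4.4%.

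**The case against.** A reader might infer that the plan puts patients in mid-follow-up into the early analysis, so that it does not estimate 6-month specificity at all. The documents do not support that. Nowhere are such patients said to be included. The endpoint is fixed at 6 months, and a restriction to completers is compatible with section 2.5. The FAS sentence foresees truncation only through unexpected loss, so it can be read as describing patients whose planned period is over. The exclusion list leans the other way. The text is ambiguous, and the conclusion has to be worded accordingly.

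A reader might also infer that sensitivity would refer to 6 months and specificity to something shorter. That is too strong. In the worked case about 8 of 48 AFib cases (17%) would be unfinished as well, against 92 of 302 AFib-free patients (30%). Both halves would mix full and partial observation, in different proportions. Nor does the text say that patients left out of a first analysis are discarded, because it does not end their follow-up.

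Three further points stand. At the 10% rate that yields 40 cases from 400 patients, the problem does not arise on expected numbers. The specificity shift of about 1 to 3 points is smaller than the planned 4% precision. It also rests on assumed accrual and false-positive timing: false positives that come early, or slower recruitment, would reduce it.

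The argument that a data cut-off belongs in the statistical analysis plan stands only in part. The article itself fixes the trigger, the FAS and the exclusions, and the first trigger does not match the endpoint's time point or the second trigger.

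**Conclusion.** The point holds as a gap in a rule that the article states. The first situation puts a follow-up condition on the AFib cases only, and each way of filling the gap misses something in the plan. Including unfinished patients departs from the 6-month endpoint and probably biases specificity upward. Analysing only completers gives a precision of 4.9% (16% AFib) or 7.5% (28%) instead of 4%.

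The precision figures need only the article's own rates and its 90% specificity. The direction of the bias needs only that per-patient false positives accumulate with time. Its size is illustrative, because neither accrual nor false-positive timing is given. The rates at which this matters, 16% and above, lie within what section 2.4 considers possible. The change should be made, but the point does not undermine the design.

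**What to change.** In section 2.5, separate the decision from the analysis. When 40 participants with recorder-detected AFib have completed follow-up, the decision on further enrolment is taken. The primary analysis is run only once every participant enrolled by that date has reached Visit 3 or left the study. Apply the same follow-up condition to AFib-positive and AFib-negative patients in both situations.

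In section 2.4, add the specificity precision to be expected if enrolment stops early. Waiting keeps every enrolled patient and recovers part or all of the lost precision (step 5 of the working), but at a 28% AFib rate it would still fall short of 4%.

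The cost is a few sentences and an analysis that comes up to about 6 months later. No extra patients or procedures are needed.
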